## Abstract

**Background:** Isolated impaired fasting glucose (i-IFG) constitutes a major group in the prediabetic spectrum among Indians, and thus it is imperative to identify effective diabetes prevention strategies. This study aims to evaluate the effects of an intensive community-based lifestyle modification program on regression to normoglycemia among women with i-IFG, compared to a control group at 24 months. The study also aims to evaluate the implementation of the intervention, via both process and implementation outcomes.

**Methods:** We will use a hybrid design (Effectiveness-implementation hybrid type 2 trial) to test the effectiveness and implementation of the lifestyle modification intervention. Effectiveness is evaluated using a randomized controlled trial among 950 overweight or obese women, aged 30 to 60 years, with i-IFG on an oral glucose tolerance test in the Indian state of Kerala. The intervention involves an intensive lifestyle modification program through group and individually mentored sessions using behavioural determinants and behavioural change techniques.  The intervention group will receive the intervention for a period of 12 months and the control group will receive general health advice through a health education booklet. Data on behavioural, clinical, and biochemical measures will be collected using standard methods at 12 and 24 months. The primary outcome will be regression to normoglycemia at 24 months, as defined by the American Diabetes Association criteria.

**Discussion**: This study will provide the first evidence on the effects of lifestyle interventions on regression to normoglycemia in people with i-IFG among Indians.

**CTRI registration:** CTRI/2021/07/035289 (30/07/2021)

## Introduction

Type 2 diabetes mellitus (T2DM), currently affects almost 537 million adults worldwide with a projected increase of nearly 50% by 2045
^
1
^. Low- and middle-income countries (LMICs) such as India are disproportionately affected, with the large majority (81%) of people with T2DM living in these countries
^
1
^. India has the second-largest number of people (74 million) living with T2DM and this is projected to increase to 125 million people by 2045
^
1
^. In addition, T2DM poses a significant economic burden in LMICs, affecting not just the health care system but also individuals and families with increased out-of-pocket spending for diabetes care
^
2
^. Therefore, much importance has been given to diabetes prevention, with a greater research focus on individuals who are at high risk for diabetes.

Prediabetes, a high-risk metabolic state for diabetes, comprises impaired fasting glucose (IFG) and impaired glucose tolerance (IGT), wherein the glucose levels are higher than those considered to be normal, but lower than the threshold for T2DM
^
3
^. A recent review of 19 studies globally showed that among those with prediabetes, the average proportions of isolated IFG (i-IFG), isolated IGT (i-IGT), and combined IFG and IGT were 43.9%, 41.0%, and 13.5%, respectively, in Caucasians, and 29.2%, 49.4%, and 18.2%, respectively, in Asians
^
4
^. A large-scale study in 15 states of India showed that i-IFG is the most common form of prediabetes among adults, with a prevalence of 21%
^
5
^. On average, nearly 5–10% of people with prediabetes develop T2DM every year, although the progression rate varies by population characteristics (including ethnicity) and the definition of prediabetes
^
6
^. With no effective intervention, nearly 70% of people with prediabetes would eventually progress to develop T2DM
^
6
^.

Lifestyle modification is recognized as an effective non-pharmacologic intervention to prevent or delay the onset of diabetes among individuals with prediabetes
^
7
^. Most landmark lifestyle modification randomized controlled trials (RCTs) for diabetes prevention have been conducted in individuals with IGT
^
8
^, with very limited evidence in the i-IFG group. Lifestyle modification in the trials for those with IGT have focused mainly on weight loss and promoting physical activity, although the intervention intensity, goals, and delivery methods have varied widely between the trials. These trials have shown that diabetes incidence could be reduced between 28.5% and 58% in the intervention group compared with the control group
^
8
^. More importantly, a clinically meaningful reduction in diabetes incidence with lifestyle modification has been shown to persist in those with IGT even after 30 years of follow-up
^
9
^.

Only a few RCTs have evaluated the effects of lifestyle modification on diabetes prevention in people with i-IFG
^
10
^. RCTs conducted among 641 overweight Japanese
^
11
^ and 578 overweight Indian adults
^
12
^ showed hazard ratios of 1.17 (95% CI 0.50-2.74, n=379) and 0.88 (95% CI 0.43-1.20, n=166) respectively, in those with i-IFG at 3 years. Similarly, a trial among 880 adults with prediabetes in the UK showed a hazard ratio of 0.52 (95% CI 0.15-1.83, n=108) at 3 years in those with i-IFG
^
13
^. The Kerala Diabetes Prevention Program (K-DPP) from India showed a relative risk of 0.95 (95% CI 0.68, 1.33) in people with i-IFG (n=579) at 2 years among 1007 high-risk individuals
^
14
^. However, the above-mentioned findings were from the sub-group analyses, which are constrained by small sample sizes, a limited number of events, and confounding
^
15
^.

While preventing the progression of prediabetes to diabetes is important, regression to normoglycemia is also essential to achieve, even if transient, as this has been shown to be significantly associated with reduction in the development of diabetes
^
10
^. To our knowledge, there are no data on regression to normoglycemia with lifestyle modification in the i-IFG group among Indians, an ethnic group with i-IFG being the most common prediabetes phenotype
^
5,
14
^. In addition to being at high risk for diabetes, individuals with i-IFG are at an increased risk of developing micro- and macro-vascular complications, and of all-cause mortality
^
6
^.

This study aims to evaluate the effects of an intensive community-based lifestyle modification program on regression to normoglycemia among women with i-IFG compared to a control group at 24 months. We will also evaluate the effects of the intervention on improving cardiometabolic risk factors. The study will use the RE-AIM framework to evaluate Reach, Adoption, Implementation and Maintenance
^
16
^ and the intervention fidelity using process measures.

This two-arm parallel group randomized controlled trial targets women as the behavioural risk factors of overweight or obesity and physical inactivity are generally higher among women, compared to men, in the Indian context
^
17
^ and the intervention outcomes reported so far are poorer among women
^
12
^ in India.

## Methods

### Study design and setting

The study uses a hybrid design (Hybrid type 2)
^
18
^ that tests the effectiveness and implementation of a lifestyle modification program. A randomized controlled trial will evaluate the effectiveness of the intervention, and the intervention implementation and fidelity will be evaluated using implementation outcomes and process measures, respectively.

The study was registered with Clinical Trials Registry, India (CTRI/2021/07/035289, on 30
^th^ July 2021). The trial will be reported in accordance with the Consolidated Standards of Reporting Trials (CONSORT) guidelines
^
19
^.

The study will be conducted in Kasaragod district of Kerala (
Figure 1). Kerala, the southernmost Indian state, has a higher prevalence of T2DM (nearly 20%) and a greater burden of several cardiometabolic risk factors than most other Indian states
^
17
^. Further, the state is in the most advanced stage of epidemiological transition in the country
^
20
^ and said to be a harbinger of the future burden of diabetes and other chronic diseases in India
^
20
^. Thus, Kerala provides an ideal place to implement and evaluate lifestyle modification programs.

**Figure 1. f1:**
[figure not shown]
Map of the study area. **A.** India political.
**B.** Kasaragod district (shaded) in the State of Kerala.
**C**. Taluks of Kasaragod district.

Figure 2 shows the CONSORT diagram of the trial. Kasaragod is the northernmost district of Kerala, with a population of 1,307,375, a sex ratio of 1079 women for every 1000 men, and a literacy rate of 90%
^
21 
^. Kasaragod has four
*taluks* (sub-district) with 777 wards (lowest administrative division with approximately 1300 individuals in each ward)
^
21
^. From these four
*taluks*, two were randomly selected, namely Hosdurg
*taluk* and Kasaragod
*taluk*. There are 465 wards in these two taluks, amongst which those wards within 20km distance from the institute were included (269 wards) considering the logistics and feasibility. Out of 269 wards, 25 wards with at least 1000 individuals in each ward were randomly selected. From these selected wards, individuals with i-IFG will be identified and recruited to the trial with a minimum of 23 participants per ward.

**Figure 2. f2:**
[figure not shown]
CONSORT diagram of the trial.

### Study participants

**
*Inclusion criteria*:** 1) Women aged 30–60 years; 2) overweight or obese (waist circumference ≥80 cm)
^
22
^; 3) no prior history of diabetes; 4) not taking any glucose-lowering medications; 5) no prior history of gestational diabetes mellitus (GDM); 6) able to read, write and speak Malayalam, the local language; 7) consents to participate in the trial; and 8) diagnosed with i-IFG (fasting plasma glucose [FPG] 5.6-6.9 mmol/l and 2-hr plasma glucose [2-hr PG] <7.8 mmol/l) on a 2-hr oral glucose tolerance test (OGTT)
^
3
^.

**
*Exclusion criteria*:** 1) Women with known T2DM; 2) having GDM; 3) prior history of GDM; 4) breastfeeding women; 5) having major chronic illnesses including mental disorders, that are likely to impede consenting and participation in the intervention program; 6) taking medications that could alter glucose metabolism (e.g., corticosteroids); and 7) diagnosed with normoglycemia, IGT, and T2DM, as per the American Diabetes Association criteria
^
3
^ on the OGTT.

### Sample size and randomization

We assumed that the cumulative incidence of regression to normoglycemia at two years would be 18% in the control group (based on unpublished data from the K-DPP trial) and that there would be a 50% relative risk in conversion to normoglycemia with the intervention. The sample size required in each study group was 475 with a type 1 error of 5%, at least 80% power, a contamination rate of 15%, and a 10% loss to follow-up. The sample size required with same estimates and 90% power in each group is 625, and will be recruited, if logistically feasible.

The estimated sample size of 950 participants will be randomly allocated in a 1:1 ratio to the control group and the intervention group using a computer-generated randomization sequence using Microsoft excel by an independent statistician not involved in the trial. The independent statistician will generate the randomized sequence and allocate the individuals to the randomized groups. The participants and the Principal Investigator (EM) will be blinded to the allocation sequence until informed written consent for study participation is obtained. The outcome assessors, data entry personnel and statisticians who analyse the data will be blinded throughout the study as they are not part of the team that delivers intervention or manage the project.

This study uses individual randomization in order to avoid the methodological challenges of cluster randomization, including the clustering effect on statistical power and selection bias, possibility of imbalanced study groups, and the dilution effect
^
23
^. Trial conduct solutions will be put in place to address potential contamination, if any, between the study groups with individual randomization. This include using different staff for each group, education of the participants against contamination
^
23
^, and getting signed nondisclosure agreement from the intervention participants regarding the type of intervention being received. Furthermore, analytical methods that adjust for contamination will also be used. We will also quantify the contamination using a treatment fidelity framework based on the criteria advocated by the Behaviour Change Consortium
^
24
^ and NICE guidance on behaviour change
^
25
^.

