### Data analysis

Data will be collected and entered using a data entry template in an ODK platform by the data collectors and managed in a cloud-based server which will only be accessed by the Principal Investigator (EM). Subsequent to the data collection, the data will be used only using a participant identity number and all the personal identifiers will be masked. Only deidentified data will be shared with other investigators, if required. Data quality will be ensured during data collection and data analysis. During the data collection, the research team will verify the data for missing values and if present, will be rectified then and there. Furthermore, randomly identified 5% of the participants data will be verified with the participants through telephone for quality check. The data from the ODK platform will be exported to SPSS and data cleaning will be done manually. Any outliers or implausible values will be identified and will be checked with participants over phone, if necessary.

The analysis will follow the intention-to-treat (ITT) principle. Characteristics of the participants at baseline will be compared between study groups using descriptive statistics. The primary outcome will be analysed using the generalized estimating equations (GEE) with an appropriate working correlation structure and a binomial family with 'log' link function to estimate the relative risk (and 95% confidence interval [CI], p value). Standard errors will be based on Huber-White sandwich estimator, which will provide valid CIs even in case of misspecification of the correlation structure
^
50
^. For secondary outcomes, continuous variables will be analysed using mixed-effects linear regression models, which will include all available data at baseline, 12 and 24 months. Study group (intervention vs. control), timepoint (follow-up vs. baseline) and a study group-by-time point interaction will be specified as fixed effects. Random effects will be specified for wards, to account for the clustered study design, and for participants, to account for correlation between the repeated measurements on the same individual. Categorical variables will be analyzed using log-binomial models. All p values reported will be 2 tailed, and a p of 0.05 will be considered statistically significant. Analyses will be performed with
Stata version 14.2 (StataCorp LP, College Station, Texas, USA). 

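### The 475 and 625 per group count contaminated women as lost, but under intention-to-treat they dilute the effect; with full transfer, power is about 76% and 86%, not 80% and 90%

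*Protocol article*

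**What the plan says.** All the design inputs are in the protocol article, under Sample size and randomization. The control assumption is that "the cumulative incidence of regression to normoglycemia at two years would be 18% in the control group". The effect is worded as "there would be a 50% relative risk in conversion to normoglycemia with the intervention". The allowances are "a contamination rate of 15" per cent and "a 10% loss to follow-up". From these the section concludes: "The sample size required in each study group was 475 with a type 1 error of 5%, at least 80% power". For the larger option it says: "The sample size required with same estimates and 90% power in each group is 625". It does not say how contamination entered the calculation, or how much of the effect a contaminated woman is assumed to gain. It adds that methods adjusting for contamination will be used as well.

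Under Data analysis: "The analysis will follow the intention-to-treat (ITT) principle", and "All p values reported will be 2 tailed".

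**The concern.** A woman lost to follow-up contributes no outcome, so dividing the required size by one minus the loss rate is right for her. A contaminated control is different. She has an outcome, and under intention-to-treat she is analysed as a control. She does not reduce the number analysed; she raises the control rate and narrows the contrast. Treating her as lost corrects for the wrong thing, and usually by too little if she gains most of the effect.

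The stake is the power claim for the primary outcome. A null result would be read against 80% or 90% power that the design may not have.

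The effect wording adds a separate difficulty. Taken literally, a 50% relative risk is a ratio of 0.5, which means fewer regressions with the intervention.

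**Working it through.** **Inputs.** From Sample size and randomization: control rate 0.18; type 1 error 5%; contamination 15%; loss 10%; 475 or 625 per group. From Data analysis: two-sided tests, intention-to-treat. Read from the context: relative risk 1.5, so the intervention rate is 1.5 × 0.18 = 0.27 and the difference is 0.09.

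**Step 1: reproduce 475 and 625.** Unpooled two-proportion formula:

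n₀ = (z₀.₉₇₅ + z_power)² × (0.18 × 0.82 + 0.27 × 0.73) / 0.09²

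This gives 334.0 (80%) and 447.1 (90%). The continuity correction is n = (n₀/4) × [1 + √(1 + 4/(n₀ × 0.09))]², which gives 355.9 and 469.1. Dividing by 1 − 0.15 − 0.10 = 0.75:

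- 80%: 355.9 / 0.75 = 474.5
- 90%: 469.1 / 0.75 = 625.5

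Both match the stated sizes almost exactly. Two other routes come near:

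| Route | 80% | 90% |
|---|---|---|
| Unpooled, continuity-corrected, ÷ 0.75 | 474.5 | 625.5 |
| Pooled, continuity-corrected (358.6, 472.3), ÷ (0.85 × 0.90) | 469 | 617 |
| Pooled, 19.35% vs 27%, 10% loss left out | 476 | 637 |

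The first two treat contamination as loss. The third dilutes correctly but drops the stated loss.

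**Step 2: the effect.** With a literal relative risk of 0.5 (9% versus 18%), the pooled formula with the same allowances gives about 294 to 329 per group for 80% power, far from 475. A relative risk of 1.5 fits.

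**Step 3: power with contamination as dilution.** Let a contaminated control gain a share t of the effect. The control rate becomes 0.18 + 0.15 × t × 0.09. The number analysed per group is 0.9 × 475 = 427.5 or 0.9 × 625 = 562.5. Then

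power = Φ{[δ√n − 1.960 √(2p̄(1 − p̄))] / √(p₁(1 − p₁) + p₂(1 − p₂))}

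For t = 1: control rate 0.1935, δ = 0.0765, p̄ = 0.23175.

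- n = 427.5: (1.582 − 1.170) / 0.594 = 0.694, power 75.6%
- n = 562.5: (1.814 − 1.170) / 0.594 = 1.085, power 86.1%

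With a continuity correction these are 73.0% and 84.5%.

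| Assumption (15% contamination, 10% loss) | 475 per group | 625 per group |
|---|---|---|
| Controls gain the full effect | 75.6% | 86.1% |
| Controls gain 70% | 80.1% | 89.6% |
| Controls gain 65% | 80.7% | 90.1% |
| Controls gain half | 82.7% | 91.5% |
| Controls gain nothing | 88.5% | 95.2% |
| 15% of the intervention arm diluted instead (18% vs 25.65%) | 77.4% | 87.5% |

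**Step 4: size needed under full transfer.** The pooled formula for 19.35% versus 27% gives 476.4 and 637.3 evaluable. Divided by 0.9 and rounded up, this is 530 and 709 randomised per group.

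**The case against.** The strongest objection is that the shortfall depends on an input the protocol does not give. It states a contamination rate, not the benefit a contaminated control receives. The intervention is a year of monthly sessions with individual goal setting, peer mentoring and a trial-specific app, and leakage is to be limited by separate staff, participant education and nondisclosure agreements. A control who hears advice from a neighbour may gain only part of the effect, and at half the effect both power claims are met. This stands. A reader might infer that 950 women give 76% power on the stated inputs alone; the document does not support that without the added assumption of full transfer. A reader might also apply 15% dilution to both arms and arrive at much lower power, but nothing in the text says contamination runs both ways.

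A second objection is that this is no miscalculation. That also stands: the sizes follow from a standard formula. What is open to criticism is the handling of contamination, which does not match the planned analysis. Nor is counting contamination as loss the only route to figures near 475 and 625, although it gives the closest match.

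A third is that contamination will be measured and adjusted for. Those analyses are additional to the intention-to-treat comparison. They help to interpret a null result but do not restore that comparison's power.

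On the effect wording, the aim is plainly more regression, so the intended 27% can be worked out. A reader might infer that the trial was powered in the wrong direction; the sizes rule that out.

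**Conclusion.** The point holds as a fault in how contamination was modelled and in the power statement that follows. Under the usual meaning of a contamination rate, where contaminated controls gain the full effect, the risk of missing a true effect is about 24% rather than at most 20% with 950 women, and about 14% rather than 10% with 1,250. If the dilution is in the intervention arm instead, power is about 77% and 88%, so both claims still fail. The 80% claim survives only if contaminated controls gain no more than about 70% of the effect, and the 90% claim only up to about 65%. The protocol makes no such partial-transfer assumption.

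These results rest on a relative risk of 1.5, 10% loss in each group and the pooled two-proportion approximation. That contamination was counted as attrition is an inference from the close match in Step 1; the protocol does not say so. The 50% relative risk is mis-stated whichever contamination model is used.

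**What to change.** In Sample size and randomization:

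1. State the effect as 18% versus 27%, relative risk 1.5.
2. Model contamination as dilution under intention-to-treat, separately from the 10% loss, and say in which arm it is expected and what share of the effect is assumed to transfer.
3. Restate the power of both sizes, with a range. For example: *With 15% of controls contaminated and 10% lost, 475 per group gives about 76% power and 625 about 86% if contaminated controls gain the full effect, and about 83% and 92% if they gain half.*

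No added enrolment is required. If the sponsor prefers to keep 80% or 90% under full transfer, the sizes are about 530 and 709 per group. Otherwise the only cost is a change of wording and a less favourable power statement. The article reports that the trial is still screening, so the correction can be made in time.

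### The stated 80% and 90% power allow for 15% contamination only if contaminated controls gain about two thirds of the effect or less; at full effect, power is about 76% and 86%

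*Protocol article*

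**What the plan says.** All the design inputs are in the protocol article under Sample size and randomization, except the sidedness and the analysis principle, which are under Data analysis.

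- Control rate: "cumulative incidence of regression to normoglycemia at two years would be 18% in the control group".
- Effect: "there would be a 50% relative risk in conversion to normoglycemia with the intervention".
- Size per group: "475 with a type 1 error of 5%, at least 80% power, a contamination rate of 15%, and a 10% loss to follow-up".
- Larger option: "The sample size required with same estimates and 90% power in each group is 625", to be recruited if logistics allow.
- Allocation: women are "randomly allocated in a 1:1 ratio to the control group and the intervention group".
- Sidedness: "All p values reported will be 2 tailed".
- Analysis: "The analysis will follow the intention-to-treat (ITT) principle".

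The sample-size section uses contamination in its usual sense. It describes measures against "potential contamination, if any, between the study groups with individual randomization", such as separate staff and nondisclosure agreements, and promises further analyses that adjust for contamination. It does not print the sample-size formula, say how the 15% entered it, or say how much of the intervention effect a contaminated woman is taken to gain.

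**The concern.** Loss to follow-up and contamination act differently on power. A woman lost to follow-up contributes no outcome, so a loss fraction c is repaired by dividing n by (1 − c). A contaminated woman is still measured and, under intention-to-treat, is still counted in the group to which she was randomized. She reduces the difference between groups. If contaminated women gain the full effect, the required n rises roughly with 1/(1 − c)².

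The stated sizes look like the product of the first rule applied to both percentages. If so, the allowance for contamination is too small, and the claim that the design keeps at least 80% or 90% power after 15% contamination is too favourable. Contamination is the main known price of individual randomization within wards, and the section presents it as already paid for. The choice between 475 and 625 per group also rests on these power figures, and readers of a null primary result would rely on them.

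**Working it through.** **Inputs.** Control rate 18%. The 50% relative effect is read as a relative risk of 1.5, so 27% with intervention. A literal relative risk of 0.5 (18% versus 9%) gives only about 290 to 380 per group at 80% power after inflation, which does not fit 475. Two-sided α = 0.05, 1:1 allocation, contamination 15%, loss 10%.

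**Step 1: the plan's own figures.** Pooled two-proportion formula, with p̄ the mean of the two rates and d their difference:

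n = [1.960·√(2p̄(1−p̄)) + z_power·√(p₁(1−p₁) + p₂(1−p₂))]² / d²

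For 18% versus 27%, p̄ = 0.225 and d = 0.09:

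- 80%: (1.960 × 0.5906 + 0.842 × 0.5871)² / 0.0081 = 336.8
- 90%: (1.960 × 0.5906 + 1.282 × 0.5871)² / 0.0081 = 450.3

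The continuity correction multiplies n by ¼[1 + √(1 + 4/(nd))]², giving 358.6 and 472.3. Candidate routes to the stated sizes:

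| Route | 80% (stated 475) | 90% (stated 625) |
|---|---|---|
| Corrected n / (0.85 × 0.90) | 469 | 617 |
| Corrected n / (1 − 0.25) | 478 | 630 |
| Uncorrected n / 0.85², 10% loss left out | 466 | 623 |
| Half-effect dilution, corrected n / 0.90 | 468 | 618 |
| Full dilution, uncorrected n / 0.90 | 529 | 708 |
| Full dilution, corrected n / 0.90 | 558 | 737 |

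The first two routes use every stated input, need no further assumption and bracket both figures. The third is close but drops the stated loss allowance. The fourth is close but needs an unstated half effect. Full dilution with the loss allowance does not fit.

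**Step 2: power of the stated sizes under full-effect contamination of controls.** The control rate becomes 0.85 × 18% + 0.15 × 27% = 19.35%. The difference falls from 9.0 to 7.65 points, and the relative risk from 1.50 to 27/19.35 = 1.40. Evaluable n is 0.9 × 475 = 427.5 and 0.9 × 625 = 562.5.

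Power = Φ{[d√n − 1.960·√(2p̄(1−p̄))] / √(p₁(1−p₁) + p₂(1−p₂))}, with p̄ = 0.23175:

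- 475: (0.0765 × 20.676 − 1.960 × 0.5967) / 0.5943 = 0.694, so 75.6%
- 625: (0.0765 × 23.717 − 1.960 × 0.5967) / 0.5943 = 1.085, so 86.1%

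Simulation gave 75.7% and 86.1%. With continuity correction the values are 73.0% and 84.5%.

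**Step 3: range over the assumption the protocol does not give.** If contaminated controls gain a share s of the effect, the control rate is 18% + 0.15 × s × 9 points. Power without continuity correction:

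| Share s | Control rate | 475 per group | 625 per group |
|---|---|---|---|
| 0 (no contamination) | 18.00% | 88.5% | 95.2% |
| 25% | 18.34% | 85.8% | 93.5% |
| 50% | 18.68% | 82.7% | 91.5% |
| 65% | 18.88% | 80.7% | 90.1% |
| 70% | 18.95% | 80.1% | 89.6% |
| 100% | 19.35% | 75.6% | 86.1% |

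Two other patterns at full effect: dilution on the intervention side only (18% versus 25.65%) gives 77.4% and 87.5%; dilution in both groups (19.35% versus 25.65%) gives 59.7% and 71.6%.

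**Step 4: the effect for which the stated power is reached.** For a true relative risk R with 15% full-effect contamination of controls, the rates are 0.18 + 0.15 × 0.18(R − 1) and 0.18R. Power of 80% at 475 needs R of about 1.53 (19.43% versus 27.54%). Power of 90% at 625 needs R of about 1.535. With continuity correction both are about 1.55.

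**The case against.** Three points weigh on the other side.

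First, a reader might infer from Step 1 that the calculation certainly treated contamination as dropout. The article does not support that. No formula is printed, no route gives exactly 475 and 625, and dilution with the loss allowance omitted comes about as close. The handling is an inference. The power result in Step 2 does not depend on it, because it tests the stated sizes directly against the stated rates.

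Second, a reader might infer that the design lacks its stated power on its own figures alone. That is also too strong. The shortfall needs contaminated controls to gain most of the effect. The intervention is a year of monthly sessions with peer mentors and a dedicated mobile application, and steps are taken to keep the groups apart, so second-hand exposure may well carry less than the full effect. At half the effect the stated powers are met. This stands, and it is why the range must be shown. But the protocol states a 15% contamination rate without any reduction, and a rate given that way is ordinarily read as 15% of women behaving like the other group.

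Third, contamination is to be measured and adjusted for. That helps in interpreting a null result, but it does not restore the power of the intention-to-treat comparison. Nor is this a detail that an article may leave to a fuller document: the inputs, sizes and powers are all printed, and the question is whether they agree.

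**Conclusion.** The power claim is not supported under the ordinary reading of a 15% contamination rate. With 15% of controls gaining the full effect, 10% lost and a two-sided 5% test, power is about 76% rather than at least 80% at 475 per group, and about 86% rather than 90% at 625. The type II error is then about 24% and 14%. The claim does hold if contaminated controls gain no more than about 70% (475) or 65% (625) of the effect, but the protocol states no such assumption and nothing in it fixes the share.

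The shortfall is about 4 points (5.5 to 7 with continuity correction). It affects neither the validity of the analysis nor the type I error, and it is equivalent to a detectable relative risk of about 1.53 to 1.54 in place of 1.50. It should be corrected, but it is not a fatal flaw.

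**What to change.** Keep 475 and 625 per group and revise the sample-size paragraph:

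1. Print the formula, including whether a continuity correction was used. State that the 10% loss removes outcomes, whereas the 15% contamination dilutes the intention-to-treat effect.
2. State what share of the effect contaminated controls are assumed to gain, and why.
3. Restate power as about 76% (475) and 86% (625) if contaminated controls gain the full effect, with the diluted target of 19.35% versus 27% (relative risk 1.40), and give the range over partial effect, for example about 83% and 92% at half the effect. Equivalently, say that under full-effect contamination 80% and 90% power are reached at a true relative risk of about 1.53 to 1.54.

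The cost is wording only, plus a slightly less favourable stated power. The article reports that the trial is still screening, so the text can be corrected before outcome data exist.
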